## Abstract

**Introduction:**

Short forms of the Montreal Cognitive Assessment (MoCA) have allowed quick cognitive screening. However, none of the available short forms has been created or validated in a Swedish sample of patients with stroke.

The aim is to develop a short-form Swedish version of the MoCA (s-MoCA-SWE) in a sample of patients with acute and subacute stroke. The specific objectives are: (1) to identify a subgroup of MoCA items that have the potential to form the s-MoCA-SWE; (2) to determine the optimal cut-off value of s-MoCA-SWE for predicting cognitive impairment and (3) and to compare the psychometric properties of s-MoCA-SWE with those of previously developed MoCA short forms.

**Methods and analysis:**

This is a statistical analysis protocol for a cross-sectional study. The study sample will comprise patients from Väststroke, a local stroke registry from Gothenburg, Sweden and Efficacy oF Fluoxetine—a randomisEd Controlled Trial in Stroke (EFFECTS), a randomised controlled trial in Sweden. The s-MoCA-SWE will be developed by using exploratory factor analysis and the boosted regression tree algorithm. The cut-off value of s-MoCA-SWE for impaired cognition will be determined based on binary logistic regression analysis. The psychometric properties of s-MoCA-SWE will be compared with those of other MoCA short forms by using cross-tabulation and area under the receiving operating characteristic curve analyses.

**Ethics and dissemination:**

The Väststroke study has received ethical approval from the Regional Ethical Review Board in Gothenburg (346–16) and the Swedish Ethical Review Authority (amendment 2019–04299). The handling of data generated within the framework of quality registers does not require written informed consent from patients. The EFFECTS study has received ethical approval from the Stockholm Ethics Committee (2013/1265-31/2 on 30 September 2013). All participants provided written consent. Results will be published in an international, peer-reviewed journal, presented at conferences and communicated to clinical practitioners in local meetings and seminars.

Strengths and limitations of this studyA short form of the Swedish version of the Montreal Cognitive Assessment will be created for the first time for use in patients with stroke.The study will use a large sample size from different acute stroke and stroke rehabilitation units across Sweden.The retrospective analysis of registry data is one limitation of the study.A high number of non-random missing Montreal Cognitive Assessment values is expected.

## Introduction

Cognitive impairment, a common sequela of stroke, has been defined as a new cognitive deficit that develops in the first 3 months after stroke and cannot be explained by other conditions or diseases.^1^ Cognitive impairment is a consequence of complex interactions between age, education and injury size and location.^2^ The prevalence of cognitive impairment in the first 3 weeks after stroke can vary between 55% and 59% depending on the time of assessment and the assessment instruments.^3 4^ Previous studies have shown that cognitive impairment after stroke is associated with higher mortality and long-term disability.^5^ Thus, early identification of cognitive impairments after stroke is important for planning individually tailored rehabilitation.

Comprehensive cognitive assessments in acute stroke units can be time and resource demanding for patients as well as for healthcare professionals. Therefore, the use of short screening tools for cognitive impairment is recommended.^6 7^ The Montreal Cognitive Assessment (MoCA) is frequently used to screen cognitive function.^7^ The MoCA targets cognitive domains such as visuospatial ability, executive function, attention, concentration, working memory, language, short-term memory and orientation.^8^ It has a good sensitivity for detecting poststroke cognitive impairment.^9 10^ To make cognitive screenings time effective, several short forms of the MoCA have been developed and tested in recent years, including a telephone version of the MoCA (T-MoCA), a short version of the MoCA that has been designed by the National Institute of Neurological Disorders and Stroke and the Canadian Stroke Network (NINDS-CSN, 5 min protocol) and the short-form MoCA (SF-MoCA).^11–19^ Different cutoffs for impaired cognition have been reported for the MoCA as well as its short forms.^11 12 15 17–20^ None of the available short forms have been developed or validated in a Swedish sample of patients with stroke.

Performance on cognitive tests after stroke can depend on premorbid cognitive reserves, which are associated with education, occupation and socioeconomic situation.^21 22^ Items of the MoCA can function differently in various cultures; therefore, cultural validation of the MoCA has been recommended for generalisability.^23^ Theoretically, this recommendation is accurate even when it comes to short forms of the MoCA. In order to have a short form of the MoCA used in a broader context as a time-effective screening instrument with good sensitivity for detecting cognitive impairment, it needs to be validated culturally within the target population.

### Study aims

The aim of this study is to develop a short-form Swedish version of the MoCA (s-MoCA-SWE) using data from Swedish stroke cohorts. The specific objectives are: (1) to identify a subgroup of MoCA items that have the potential to form the s-MoCA-SWE; (2) to determine the optimal cut-off value of s-MoCA-SWE for predicting cognitive impairment and (3) to compare the psychometric properties of s-MoCA-SWE with those of T-MoCA, NINDS-CSN and SF-MoCA.

## Methods and analysis

### Study design

This is a cross-sectional, exploratory study. Two datasets will be used: Väststroke, a local stroke registry from Gothenburg, Sweden and Efficacy oF Fluoxetine—a randomisEd Controlled Trial in Stroke (EFFECTS), a randomised controlled trial.^24^

The Väststroke register comprises data from three stroke units in Sahlgrenska University Hospital. The data in Väststroke were gathered within the scope of the Physical Activity Pre-Stroke In GOThenburg (PAPSIGOT) project.^25^ The Väststroke registry was linked to the Riksstroke, a national quality register for stroke care in Sweden, via each patient’s unique personal identification number.^26^ The statisticians at Riksstroke merged the data. The Väststroke data from 1 November 2014 to 30 June 2019 were retrieved.

The EFFECTS was a randomised, double-blind, placebo-controlled clinical trial conducted in 35 stroke or rehabilitation units in Sweden.^24^ The inclusion period was from 20 October 2014 to 28 June 2019.^24^ Briefly, patients aged ≥18 years and diagnosed with ischaemic or haemorrhagic stroke confirmed by brain imaging were included. Detailed information about EFFECTS can be found elsewhere.^24^

### Study sample

The Väststroke dataset comprises data on 6493 patients; the EFFECTS dataset comprises data on 1500 patients (online supplemental figure). The two datasets will be aligned.

10.1136/bmjopen-2021-049035.supp1Supplementary data

The inclusion criteria are as follows:

Age ≥18 years at stroke onset.A diagnosis of stroke according to the International Classification of Diseases-10: intracerebral haemorrhage (I61), cerebral infarction (I63) and stroke, not specified as haemorrhage or infarction (I64).Patients with a previous stroke and/or transient ischaemic attack (TIA).A complete MoCA (0–30 p).

The exclusion criterion was as follows:

Duplicate registration on the Väststroke and EFFECTS datasets (duplicates will be removed from the Väststroke dataset).

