### Missing data

For descriptive statistics, data on all included patients will be used. The proportion of missing values will be provided for each baseline variable.

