### Patient and public involvement statement

The patients and the public were not involved in the design of the protocol.

Cognition has been identified by patients, their caregivers, and healthcare professionals as one of the most important research areas in stroke.^35^ Furthermore, many patients have reported unmet needs regarding problems with cognitive functions, such as memory, concentration and speaking/reading.^36^ Thus, early identification of cognitive impairment is important.

Patients with stroke can find cognitive assessments fairly burdensome in acute stroke and would prefer short tests if possible. By developing s-MoCA-SWE, we hope to have a simpler and more efficient cognitive screening tool that can be used during acute and subacute stroke. Theoretically, this would lead to a higher proportion of patients who receive the recommended cognitive screenings.

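### Every analysis is confined to complete MoCAs although many non-random missing MoCAs are expected, so the predictive values above all describe a selected group, and nothing planned addresses this

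*Protocol article*

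**What the plan says.** - Study sample: the source data are given as "The Väststroke dataset comprises data on 6493 patients; the EFFECTS dataset comprises data on 1500 patients". One inclusion criterion is "A complete MoCA (0–30 p".
- Strengths and limitations (in the abstract block): "A high number of non-random missing Montreal Cognitive Assessment values is expected". No rate and no reasons are given.
- Missing data: the section has two statements, "For descriptive statistics, data on all included patients will be used" and "The proportion of missing values will be provided for each baseline variable".
- Objectives 2 and 3: the cut-off is chosen for good sensitivity against MoCA ≤25 p. Sensitivity, specificity, PPV, NPV and Youden's index are then reported with 95% CIs. No other analysis population is named.
- Patient and public involvement statement: the hope is for a "simpler and more efficient cognitive screening tool that can be used during acute and subacute stroke", followed by "Theoretically, this would lead to a higher proportion of patients who receive the recommended cognitive screenings".

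**The concern.** The missingness that the article warns about concerns the MoCA itself. Everyone who is included has a complete MoCA by definition, so a missing-data section limited to included patients cannot reach it. What is fixed is a complete-case analysis with no stated comparison, weighting or sensitivity analysis and no narrowing of the conclusion.

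PPV and NPV depend directly on the prevalence of MoCA ≤25 p in the analysed group. Sensitivity, specificity and a cut-off set by sensitivity can also shift with the mix of patients. If patients with a complete MoCA differ in cognition from the rest, these figures will not carry over to acute and subacute stroke at large. For a screening tool the NPV matters most, because it tells staff how far to trust a negative result.

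**Working it through.** The article states no completion rate, expected prevalence in the sample, or target predictive value, so there is no figure to reproduce. Two illustrations on assumed inputs show which results are exposed.

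**1. Prevalence alone.** Assumed sensitivity Se = 0.85 and specificity Sp = 0.80, both held fixed; p is the prevalence of impairment.

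PPV = Se·p / [Se·p + (1 − Sp)(1 − p)]; NPV = Sp(1 − p) / [Sp(1 − p) + (1 − Se)p]

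At p = 0.55, the lower end of the range in the Introduction:
- PPV = 0.4675 / (0.4675 + 0.0900) = 0.84
- NPV = 0.3600 / (0.3600 + 0.0825) = 0.81

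At p = 0.59, the upper end, PPV is 0.86 and NPV 0.79. Within the article's own range the change is small.

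Now let completers have p = 0.57 and let 40% of patients be non-completers with prevalence q (both assumed). Overall prevalence is 0.6 × 0.57 + 0.4 × q.

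| q in non-completers | Overall p | PPV, all | NPV, all |
|---|---|---|---|
| 0.45 | 0.342 + 0.180 = 0.522 | 0.4437 / 0.5393 = 0.82 | 0.3824 / 0.4607 = 0.83 |
| 0.57 | 0.570 | 0.85 | 0.80 |
| 0.70 | 0.342 + 0.280 = 0.622 | 0.87 | 0.3024 / 0.3957 = 0.76 |
| 0.85 | 0.342 + 0.340 = 0.682 | 0.90 | 0.2544 / 0.3567 = 0.71 |

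The row q = 0.57 is also what the study would report from completers. The row q = 0.45 shows the bias reversing if the untested patients are the less impaired ones.

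**2. Letting the patient mix change as well.** A simulation of 2,000,000 patients, all inputs assumed: MoCA normal with mean 24 and SD 4.5, treated as continuous, impaired if ≤25; short score = 0.45 × MoCA + normal error with SD 1.2; log-odds of completion = 0.3 + b × (MoCA − 24). The cut-off is set for 90% sensitivity in completers and then applied to the other groups. Prevalence in all patients is 0.59.

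| b | Complete | Prevalence, completers | Cut-off from completers (from all: 11.63) | Group | Se | Sp | PPV | NPV |
|---|---|---|---|---|---|---|---|---|
| 0 | 0.575 | 0.59 | 11.63 | completers | 0.90 | 0.735 | 0.83 | 0.84 |
| | | | | all | 0.90 | 0.735 | 0.83 | 0.84 |
| 0.2 | 0.564 | 0.45 | 11.84 | completers | 0.90 | 0.71 | 0.72 | 0.90 |
| | | | | all | 0.92 | 0.69 | 0.81 | 0.86 |
| | | | | non-completers | 0.94 | 0.62 | 0.89 | 0.76 |
| 0.4 | 0.548 | 0.36 | 12.01 | completers | 0.90 | 0.67 | 0.61 | 0.92 |
| | | | | all | 0.94 | 0.65 | 0.79 | 0.88 |
| | | | | non-completers | 0.96 | 0.50 | 0.92 | 0.66 |

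If completion is unrelated to cognition (b = 0), nothing is biased. If poorer cognition lowers completion, completers overstate NPV and understate PPV, and also understate sensitivity at the chosen cut-off. The cut-off moves by 12.01 − 11.63 = 0.38 points at most. Item selection was not simulated.

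**The case against.** **The criterion is necessary.** The reference is MoCA ≤25 p and every short form is a sum of MoCA items, so without a complete MoCA there is no reference. This stands. A reader might infer that the criterion should be dropped; it should not.

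**The limitation is disclosed, the study is called exploratory, and an article may leave sensitivity analyses to a fuller plan.** The disclosure is real, and nothing is hidden. But this article calls itself a statistical analysis protocol and contains a Missing data section whose stated scope excludes the problem that its own limitations list names. That is a badly fixed choice rather than an omitted detail. The supplementary figure and tables are not shown and may describe the excluded patients, so it cannot be said that they are never described. A flow chart or table would still not adjust the PPV, NPV or cut-off.

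**Direction is unknown.** A reader might infer that the sample is enriched for milder patients able to finish the long test. The article calls the missingness non-random but gives no reasons for it. Some MoCAs may be missing for logistic reasons or because a patient seemed intact, and a score range of 0–30 excludes nobody for scoring low.

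**Purpose.** A reader might also conclude that the study fails its purpose because it drops the very patients the short form should reach. Wider screening is worded as a theoretical hope and is not among the three objectives. The Introduction also gives staff time as a reason for short tools, so screening could widen among patients who could finish the full MoCA.

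**Weights are a partial remedy.** In the simulation, completion depends on cognition itself; covariate weights remove only what the covariates explain. This stands and should be stated with the results.

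**Conclusion.** The concern holds in a limited form. The complete-MoCA rule, the expected non-random missingness and a missing-data section confined to included patients together mean that predictive values, and to a lesser extent sensitivity, specificity and the cut-off, are estimated in a selected group while the tool is meant for acute and subacute stroke generally.

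The size and direction cannot be determined from the document. In the illustrations with more impairment among non-completers, NPV for all patients was 0.04 to 0.09 below the value in completers, and the cut-off moved by less than one point. Those figures rest on assumed accuracy, an assumed share of non-completers and an assumed link between cognition and completion. With no such link the difference is zero, and with the opposite link it changes sign. No effect on the choice of items has been shown.

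**What to change.** Keep the complete-MoCA criterion and add three things to the analysis plan:

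1. Compare patients with and without a complete MoCA in the merged data (6493 + 1500 less duplicates) on age, NIHSS, reperfusion treatment, previous stroke/TIA and dataset.
2. Report Objectives 2 and 3 with inverse-probability-of-completion weights, built from the same variables, as a sensitivity analysis beside the unweighted results. State that the weights correct only for missingness that these variables explain. Preferably give results by dataset too: the merged set mixes a local registry with a consented trial, and because Väststroke holds first-ever strokes only, previous stroke is largely tied to dataset.
3. Limit the conclusions on PPV, NPV and cut-off to patients who have a complete MoCA.

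Completion per item is an optional addition, possible only if items from partial MoCAs are registered, which the article does not say.

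The cost is some wording and one extra analysis on data already held. The weighted results will have somewhat wider confidence intervals and will rely on a completion model.

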### Study procedure

Väststroke data were registered by healthcare professionals working in stroke units. The MoCA was administered by occupational therapists. Occupational therapists at stroke units have regular workshops and peer reviews regarding the administration and interpretation of the MoCA. In the EFFECTS, the patients were enrolled in the stroke and rehabilitation units between 2 and 15 days after stroke onset. Cognitive screening was performed by study personnel such as nurses or physicians at the local centre, without any formal training of the instrument; sometimes, the assessment by the local occupational therapist was used. Detailed information about the EFFECTS study is available elsewhere.^27^ Cognitive screening was performed during the acute and early subacute phases of stroke.

### Study variables

Only the variables available in both the Väststroke and EFFECTS datasets will be used. Detailed information on all variables that will be included in the study, their categories, and coding for the merged datasets are presented in online supplemental table 1.

The MoCA is a valid and reliable instrument for cognitive screening in the acute and subacute phases of stroke.^8–10^ The total MoCA score ranges between 0 and 30 points (p); 1 p for a maximum of 12 years of education can be added to the total score. A score of ≤25 p indicates cognitive impairment.^8^ MoCA items were registered in the datasets as follows:

Orientation (range, 0–6 p).Delayed recall (range, 0–5 p).Visuospatial/executive functions (range, 0–5 p): trial (1 p)+cube (1 p)+clock (3 p).Naming of three animals (range, 0–3 p).Digit span, two tasks (range, 0–2 p).Repetition of two sentences (range, 0–2 p).Categories, two tasks (range, 0–2 p).Serial 7 (range, 0–3 p).Fluency (range, 0–1 p).Tap on A (range, 0–1 p).

Stroke severity at onset was assessed using the National Institutes of Health Stroke Scale (NIHSS).^28^ The NIHSS comprises 15 items with varying score ranges per item. The total NIHSS score is 0–42 p, with a higher score indicating a more severe stroke.^28^

Reperfusion treatment will be categorised as both thrombolysis and thrombectomy, only thrombolysis or only thrombectomy.

Information about a previous stroke and/or TIA was recorded (yes, no or unknown). The Väststroke register comprises patients with a first-ever stroke, however, patients with previous TIA were included. In the EFFECTS study, patients could have a prior stroke and/or TIA, and these two conditions could not be distinguished.

#### Aggregated variables

The T-MoCA is a short version of the MoCA that is based on the following items: delayed recall, digit span, list letters, serial 7, sentence repetition, fluency, abstraction and orientation.^14^ The total T-MoCA score is 22 p. The reported threshold for impaired cognition is ≤18 p.^14^

The NINDS-CSN is based on items such as delayed recall, fluency, and orientation.^15 17–19^ The total NINDS-CSN score is 12 p. The suggested thresholds for impaired cognition are ≤9 p,^13 15^ ≤10 p^16^ and ≤6 p.^17 29^

The SF-MoCA is based on items such as delayed recall, serial 7 and orientation.^11 12^ The total SF-MoCA score is 14 p, and a cut-off of ≤8 p has been suggested as an indicator for impaired cognition.^11 12^

### Statistics

Data will be presented as the mean and SD, median and IQR, minimum–maximum (min–max), number (n) and proportion (%) (online supplemental tables 2 and 3). The OR and 95% CI will be presented when appropriate. The significance level for the statistical tests will be set at α=5%. All statistical tests will be two tailed.

#### Objective 1

Two different approaches will be used to identify the MoCA items that have the potential to form the s-MoCA-SWE: exploratory factor analysis^30 31^ and boosted regression tree.^32^

Exploratory factor analysis is a dimension-reduction method with good sensitivity for identifying the latent connections between variables. Exploratory factor analysis will be performed in several steps. First, the correlations between the MoCA items will be calculated. Second, the results of Bartlett’s and Kaiser-Meyer-Olkin tests will be evaluated; values lower than 0.05 and greater than 0.7, respectively, are desirable. Third, the number of factors will be determined based on the scree plot and parallel analysis scree plot of eigenvalues. A factor-extraction method will be chosen, and a decision about rotation will be made based on the results of the previous steps. MoCA items with loading >0.6 will be chosen as having the potential to enter the s-MoCA-SWE.^31^

Boosted regression tree is a supervised machine-learning algorithm. In the boosted regression tree algorithm, modelling trees are grown sequentially (eg, each tree is grown based on the information from the previously grown trees and each tree is fit to the residuals from the previous tree). For this analysis, the dataset will be split into training (80%) and test (20%) datasets. The s-MoCA-SWE boosted regression tree will be developed based on the training dataset, and tuning parameters such as the number of trees (B), shrinkage parameter (λ) and interaction depths (d) will be chosen based on 10-fold cross-validation and bootstrapping. The MoCA items with the potential to build an s-MoCA-SWE will be chosen based on the boosted regression tree model with adjusted tuning parameters and variable coefficients >5.0. The s-MoCA-SWE developed based on the training dataset will be further tested on the test dataset.

The decision between the set of MoCA items derived from exploratory factor analysis and that derived from the boosted regression tree algorithm will be made by applying binary logistic regression analysis. The sets will be entered as independent variables and tested using different regression models. The dependent variable will be dichotomised MoCA (≤25 p for impaired cognition).^8 33^ The s-MoCA-SWE version with the highest sensitivity and classification accuracy for cognitive impairment will be analysed in objective 2.

#### Objective 2

To find the optimal cut-off value of s-MoCA-SWE for classifying patients with and without cognitive impairment, binary logistic regression analysis will be performed. The MoCA cut-off of ≤25 p for impaired cognition will be the reference output,^8 33^ and the s-MoCA-SWE full score will be the independent variable. The cut-off value of s-MoCA-SWE will be chosen based on its good sensitivity for identifying patients with cognitive impairment.

#### Objective 3

Four cross-tables will be evaluated. The reference variable will be dichotomised MoCA (≤25 p for impaired cognition).^8 33^ The index variables will be dichotomised s-MoCA-SWE (according to the results from Objective 2), T-MoCA (≤18 p for impaired cognition),^14^ NINDS-CSN (≤9 p for impaired cognition)^13 15^ and SF-MoCA (≤8 p for impaired cognition).^11 12^ The psychometric measurements of sensitivity, specificity, positive predictive value, negative predictive value and Youden’s index with 95% CI will be evaluated.

Receiving operating characteristic curve analysis will be performed. The full scores of s-MoCA-SWE, T-MoCA, NINDS-CSN and SF-MoCA will be entered as test variables, and the dichotomised MoCA (≤25 p for impaired cognition) will be entered as the state variable.^8 33^ The areas under the curve will be interpreted as follows: 0.7–0.9, moderate accuracy and 0.5–0.7, low accuracy.^34^

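### Objective 1 chooses between the two item sets on model sensitivities that need not be those of the summed score used in Objectives 2 and 3

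*Protocol article*

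**What the plan says.** All of this is in the Statistics section of the protocol article.

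- **Objective 1, what is decided.** The choice is between two groups of items: "The decision between the set of MoCA items derived from exploratory factor analysis and that derived from the boosted regression tree algorithm".
- **Objective 1, how.** Binary logistic regression, with total MoCA of 25 or less as the outcome: "The sets will be entered as independent variables and tested using different regression models".
- **Objective 1, criterion.** "The s-MoCA-SWE version with the highest sensitivity and classification accuracy for cognitive impairment will be analysed in objective 2". No probability threshold is given for this sensitivity.
- **Objective 2, form of the tool.** "the s-MoCA-SWE full score will be the independent variable".
- **Objective 2, cut-off.** "The cut-off value of s-MoCA-SWE will be chosen based on its good sensitivity for identifying patients with cognitive impairment". This step follows the choice of set.
- **Objective 3, form of the tool.** "The full scores of s-MoCA-SWE, T-MoCA, NINDS-CSN and SF-MoCA will be entered as test variables".

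**The concern.** Objective 1 speaks of sets of items as independent variables, in the plural. Objective 2 speaks of one score as the independent variable. Where the authors mean the score they name it, so item-level entry is the natural reading of Objective 1. A logistic model with separate items estimates one coefficient per item and classifies by a weighted equation. That equation is not used in Objectives 2 or 3.

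Two things then separate the deciding sensitivity from that of the tool. One is the weighting. The other is the operating point: the sets are ranked at an unstated model threshold, before the tool has a cut-off. The second holds even if set totals were meant.

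This step fixes which instrument is developed, and no later step reopens it. What is at stake is that the set which does less well as a summed score is taken into Objectives 2 and 3.

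**Working it through.** **1. Is the full score a plain sum?** The protocol does not say so for the s-MoCA-SWE, but it can be checked for the comparators. Item ranges come from Study variables and short-form totals from Aggregated variables. List letters is taken as tap on A, and abstraction as categories.

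- MoCA: 6+5+5+3+2+2+2+3+1+1 = 30, as stated.
- T-MoCA: 5+2+1+3+2+1+2+6 = 22, as stated.
- NINDS-CSN: 5+1+6 = 12, as stated.
- SF-MoCA: 5+3+6 = 14, as stated.

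All three comparators are unweighted sums. Objective 3 treats the s-MoCA-SWE full score in the same way, and no weighting is mentioned anywhere.

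**2. How far apart can the weighted model and the sum be?** The protocol gives no item distributions, so these are assumptions: one common factor, loading 0.65, assumed item difficulties, n = 200,000, giving a mean MoCA of 22.6, SD 4.7 and 69% impaired. Each set was fitted twice, as logit P = a + Σ bⱼ·itemⱼ and as logit P = a + b·(Σ itemⱼ), both classified at P = 0.5 (also assumed).

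| Items | Rule | Sensitivity | Specificity | Accuracy |
|---|---|---|---|---|
| Recall, serial 7, orientation | weighted | 0.878 | 0.793 | 0.852 |
| | sum | 0.936 | 0.645 | 0.847 |
| Recall, fluency, orientation | weighted | 0.889 | 0.739 | 0.843 |
| | sum | 0.936 | 0.614 | 0.837 |

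The sensitivity gaps are 5.8 and 4.7 points. The other five sets tried gave identical results to three decimals.

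**3. How often does the ranking of two sets change?** Three simulations, each on its own assumed inputs:

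- 160 sets of 10–16 points, n = 6,000, 56–70% impaired, five runs: sensitivity ranking changed in 9–15% of pairs, accuracy in 1–2%, AUC in under 1%. Where the sensitivity ranking changed, the median loss was 1.4–2.5 points and the 90th percentile 4–8. The extreme differences for a single set were −15 and +12 points.
- 150 random scenarios of n = 4,000 with eight sets each, loadings 0.4–0.85: sensitivity ranking changed in 19% of pairs, accuracy in 3%. Weighted minus sum sensitivity had median 0 and 95% range −4.7 to +3.8 points.
- A further run with about 77% impaired: sensitivity ranking changed in about 18% of pairs, AUC in under 1%.

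**4. Is the gap due to the weights or the threshold?** For the summed recall, serial 7 and orientation score in step 2:

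| Cut-off | Sensitivity | Specificity |
|---|---|---|
| ≤10 | 0.684 | 0.974 |
| ≤11 | 0.836 | 0.867 |
| ≤12 | 0.936 | 0.645 |
| ≤13 | 0.985 | 0.331 |

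P = 0.5 puts the sum at ≤12. The weighted model, at specificity 0.793, lies between ≤11 and ≤12. Straight-line interpolation at that specificity gives (0.867 − 0.793)/(0.867 − 0.645) = 0.333, and 0.836 + 0.333 × (0.936 − 0.836) = 0.869. Against 0.878 for the weighted model, about 0.9 of the 5.8 points remains. The rest is where the threshold falls on a coarse integer score.

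The further run in step 3 agrees. Sensitivity at P = 0.5 disagreed with the sum score's AUC ranking in 26% of pairs when items were weighted and in 31% when they were summed. Summing alone does not cure the problem.

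**The case against.** The strongest reply is that item-level entry is an inference. The text also allows one total per set in one model per set, and a condensed article may leave that to a fuller plan. This stands as far as it goes: the weighting point is conditional on the natural reading. It does not remove the point, because the article states the order of steps itself, and on either reading sets are ranked on sensitivity before a cut-off exists.

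Second, the harm may be small. The reference is itself the sum of all items, so fitted weights can be nearly equal. Accuracy is also part of the criterion, and its ranking hardly changes. Multiplying the first simulation's change rate by its median loss gives 0.09 × 1.4 ≈ 0.1 to 0.15 × 2.5 ≈ 0.4 points per decision, a rough figure since it uses medians. The simulated pairs are also arbitrary sets, not two data-derived ones. This stands and limits the weight of the point. However, the plan does not say which criterion prevails when sensitivity and accuracy disagree, so sensitivity may decide.

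Three stronger readings are tempting and are not supported:

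- A reader might infer that the deciding sensitivity is never the tool's. In five of seven example sets it was the same.
- A reader might infer that the reported performance of the s-MoCA-SWE will be wrong. Objective 3 evaluates the dichotomised form and its full score directly, so the risk lies in which set is chosen.
- A reader might infer that the 20% test-set check examines only the fitted tree. The protocol says "The s-MoCA-SWE developed based on the training dataset will be further tested on the test dataset", which names the short form. An earlier phrase ties that name to the tree, so some ambiguity remains, but no defect is stated.

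**Conclusion.** The point holds in a limited form. On the natural reading, Objective 1 selects an item set on the sensitivity and accuracy of separately weighted models at an unstated threshold, whereas the tool is a summed score at a cut-off set later. The deciding sensitivity need not be the tool's, and a weaker set could go forward.

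The size is uncertain: roughly 10–20% of simulated pairs changed order on sensitivity, with accuracy and AUC orderings almost unchanged. These figures rest on assumed item difficulties and loadings and on classification at P = 0.5, none of which the protocol gives. They show what is possible, not what will happen in these data. The main driver is the uncontrolled operating point and the weighting is secondary.

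**What to change.** In Objective 1, compute the unweighted sum score of each candidate set and enter that one score in the logistic model, as Objective 2 already does. Compare the two sets by the AUC of the sum score, or by sensitivity at a cut-off chosen by the same rule for both (for example matched specificity), and not by sensitivity at a default model threshold. If set totals were always intended, the same sentence removes the ambiguity.

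The cost is one or two sentences and a simpler analysis. Stated accuracy may fall slightly: in the first simulation the sum lost 0.2 percentage points on average against the weighted model.
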